## Abstract

**Background:**

Exercise therapy for knee pain and osteoarthritis remains a key element of conservative treatment, recommended in clinical guidelines. Yet systematic reviews point to only modest benefits from exercise interventions.

One reason for this might be that clinical trials tend to use a one-size-fits-all approach to exercise, effectively disregarding the details of their participants' clinical presentations. This uncontrolled before-after study (TargET-Knee-Pain) aims to test the principle that exercises targeted at the specific physical impairments of older adults with knee pain may be able to significantly improve those impairments. It is a first step towards testing the effectiveness of this more individually-tailored approach.

**Methods/Design:**

We aim to recruit 60 participants from an existing observational cohort of community-dwelling older adults with knee pain. Participants will all have at least one of the three physical impairments of weak quadriceps, a reduced range of knee flexion and poor standing balance. Each participant will be asked to undertake a programme of exercises, targeted at their particular combination and degree of impairment(s), over the course of twelve weeks. The exercises will be taught and progressed by an experienced physiotherapist, with reference to a "menu" of agreed exercises for each of the impairments, over the course of six fortnightly home visits, alternating with six fortnightly telephone calls. Primary outcome measures will be isometric quadriceps strength, knee flexion range of motion, timed single-leg standing balance and the "Four Balance Test Scale" at 12 weeks. Key secondary outcome measures will be self-reported levels of pain, stiffness and difficulties with day-to-day functional tasks (WOMAC). Outcome measures will be taken at three time-points (baseline, six weeks and twelve weeks) by a study nurse blinded to the exercise status of the participants.

**Discussion:**

This study (TargET-Knee-Pain) is the first step towards exploring whether an impairment-targeted approach to exercise prescription for older adults with knee pain may have sufficient efficacy to warrant further testing. If warranted, future randomised clinical trials may compare this approach with more traditional one-size-fits-all exercise approaches.

**Trial registration:**

Current Controlled Trials ISRCTN61638364.

## Background

Knee pain, associated with osteoarthritis (OA), is a common disabling problem [1]. Most patients are managed in primary care, where exercise is considered to be a core first-line treatment [2]. Clinical guidelines support the overall effectiveness of exercise in knee and hip OA, but highlight the lack of evidence around the practical aspects of exercise delivery, including which exercises work best for whom [3-7]. Likewise, clinical trials support exercise programmes supervised by physiotherapists, in terms of reduction in knee pain and improvement in function [8-10]. However, systematic reviews often show, at best, small to moderate beneficial effects of exercise [6,7,11-14]. One potential reason for this may be that many of these clinical trials have tended to adopt a one-size-fits-all approach, whereby patients receive similar exercise interventions, regardless of the nature of their impairments. Instead, the MOVE Consensus has recommended that exercise therapy for OA of the hip or knee should be tailored to the individual patient [3]. One approach to doing this is to target exercises at specific and potentially-reversible physical impairments that are common in knee OA and are known to be associated with pain and disability [15-21]. But although evidence-based recommendations on rehabilitation interventions recommend strengthening, stretching and functional exercises, such as standing balance, for knee OA [22], there are currently no published trials that have specifically used an impairment-targeted exercise approach with this population.

In this paper, we present the protocol for a proof-of-principle study (TargET-Knee-Pain) to explore whether, and to what degree, an impairment-targeted approach to home-based exercise prescription can improve quadriceps strength, range of movement at the knee, and balance in older adults with knee pain and OA. This is the first stage towards determining the effectiveness of such impairment-targeted treatment approaches. As a secondary aim, this study will endeavour to determine to what degree any improvements in these factors may be reflected in corresponding improvements in self-reported knee pain, stiffness, and functional limitation.

## Methods/Design

### Design

Single-centre, uncontrolled before-after study.

### Setting

General population; based in participants' own homes.

### Sample

The sampling frame for this study will be existing participants in an established observational cohort study of knee pain and osteoarthritis, known as The Clinical Assessment Study of the Knee - CAS(K) [23,24]. CAS(K) participants were originally recruited from the registers of three general practices in North Staffordshire between 2002 and 2003. All were aged 50 years and older and reported knee pain within the previous 12 months. Participants have been followed up at 18-month intervals. We aim to recruit 60 participants to our study from a conservatively estimated population of 314 due to attend for repeat follow-up six years after their baseline assessments. Power calculations, based on observed effect sizes in previous trials of exercises for patients with OA of the knee, suggest that a sample size of 60 individuals would be capable of detecting an 8° improvement in the degree of knee flexion or an 8 Kg improvement in quadriceps strength with approximately 86% power, given a Type 1 error rate of 5% [25,26].

### Eligibility criteria

Potential participants in our study will be attendees at the CAS(K) 6-year-follow-up research assessment clinics, who are men and women, all aged 56+ years with a history of knee pain. To be included in this study, they will have measurements for at least one of the target impairments (quadriceps strength, degree of knee flexion and single-leg standing balance) that fall below the lowest quartile of age- and gender-stratified values recorded at the baseline assessments between 2002 and 2003 (Table 1). In order to be considered for inclusion in the study, individuals must be willing and able to commit to a programme of exercises for a 12-week period.

**Table 1 T1:** Age and gender thresholds for study inclusion

	Male	Female
Range of knee joint flexion		
55-64 years	< 128°	< 127°
65-74 years	< 125°	< 122°
75+ years	< 120°	< 117°
		
Isometric quadriceps strength (kilograms force)		
55-64 years	< 18.1	< 11.3
65-74 years	< 17.2	< 9.4
75+ years	< 13.9	< 9.0
		
Single-leg standing balance (seconds)		
55-64 years	< 8	< 5
65-74 years	< 3	< 3
75+ years	< 2	< 2

The exclusion criteria are: total knee replacement of either knee joint; an existing diagnosis of inflammatory arthropathy; lower limb weakness from neurological conditions; receiving medication that adversely affects standing balance; open wounds on the anterior aspect of either distal shin; a self-report of unstable angina or uncontrolled hypertension/hypotension; an inner ear problem that compromises standing balance; no mobile or home telephone; unavailability for fortnightly home visits or telephone contact for the whole of a given working week of their potential involvement in the study; an inability to transfer independently from lying to sitting or from sitting to standing; currently receiving physiotherapy for their knee problem.

### Recruitment

Potential participants will be identified when they attend the CAS(K) 6-year follow-up research assessment clinics at a local community hospital. Their measurements for the three target impairments will be compared to the thresholds in Table 1. If a CAS(K) participant has a measurement for one or more of the target impairments that falls below one of the thresholds, he/she will be approached by the study nurse at the end of the research assessment clinic. The study nurse will explain the study in brief, provide the person with an information leaflet and seek permission to contact them by telephone to discuss their potential involvement in the study more fully.

If verbal consent to further telephone contact is given, the study nurse will contact potential participants, following a minimum 24 hour cooling-off period, in order to assess their willingness and suitability to participate. If an individual is willing and eligible to participate in the study, their agreement will be sought to arrange a time for the study nurse to visit them in their own home to undertake written consent and take baseline measurements. The recruitment process is summarised in the flowchart in Figure 1.

**Figure 1 F1:**
[figure not shown]
**Flowchart of recruitment process**.

### Consent procedure

The study nurse will seek written informed consent at the initial home visit to each potential participant, explaining the study in detail and answering any questions. Consent will be sought for the following aspects of the study:

• Practising of daily home exercises, and keeping of a daily exercise diary.

• Study nurse visits in weeks 1, 6 and 12 of the study (Figure 2), involving measurement of quadriceps strengths, degree of knee flexion and standing balance, and completion of a self-report questionnaire, taking 10-20 minutes.

**Figure 2 F2:**
[figure not shown]
**Schematic diagram of physiotherapist and nurse home visits and telephone calls for the 12 weeks of each participant's involvement in the study**.

• Six fortnightly home visits from a physiotherapist (Figure 2), lasting approximately 45 minutes each, involving repeated measurement of the target impairment(s) and progression of the exercises, and alternating with fortnightly telephone calls (Figure 2).

### Interventions

In each case the study intervention will last for 12 weeks. Three exercise packages have been developed with reference to published literature (one for each of the three target impairments): one for quadriceps strengthening, one for knee flexion stretches, and one for balance retraining. These exercise packages systematically progress each of the exercises through photographically-illustrated stages. Details of the packages are available as Additional files 1, 2 and 3. Participants will be assigned to receive one or more of these exercise packages, based on whether their measurements for either leg for the corresponding target impairments fall below the thresholds in Table 1. The exercises will be selected and the level-of-difficulty tailored to the abilities of the individual participant on the basis of the assessment by a study physiotherapist during the first physiotherapist home visit. This assessment will consist of a standardised clinical history taking and physical assessment, together with measurement of the target impairment(s). Selection and tailoring of the exercises will take the following factors into account:

• The presence and degree of the three impairment(s).

• The safety of the participant.

• Participant ease of performance when practising the exercises under the supervision of the physiotherapist.

• The preferences, motivations and concerns of the individual participant.

The dosage and frequency of the exercises will be decided by negotiation with the individual participant. The physiotherapist will also employ the following elements of advice and reassurance when teaching the exercises to the participants:

• Explicit identification of activities of daily living that could be improved by an improvement in the identified impairment(s).

• Education regarding the importance of strong quadriceps and/or good flexion range of motion and/or good balance both to the health of the knee joints and to overall function.

• Advice and reassurance regarding the expected adverse effects of the exercises, such as temporary pain and stiffness, including advice about the benign nature of these side-effects and the use of ice, heat and simple analgesia to manage them.

• Reassurance that the individual can contact one of the study physiotherapists by telephone at any time regarding any queries or concerns.

Monitoring of participants' progress and appropriate progression of the exercise programme accordingly will be achieved through the fortnightly physiotherapist home visits, alternating with fortnightly telephone calls.

Adherence to the exercise programmes will be optimised in the following ways:

• By the physiotherapist cultivating a clinical partnership of shared decision-making with the participant that takes into account their individual preferences, motivations and concerns.

• By weekly physiotherapist contact with each of the participants, by either home visit or telephone conversation.

By an emphasis on positive reinforcement.

• By recording participants' progress with each of the relevant impairments at each home visit using pin-up wall-chart graphs.

• By encouraging participants to complete daily exercise diaries, which include details of which exercises were done how many times and how often, and any comments about the exercises and their performance.

In accordance with good clinical governance, details of the clinical history and findings from the physical examination of the participants will be recorded in writing in a standardised clinical notation booklet, together with participants' progress notes, so that the details of every physiotherapist contact with the participants are recorded.

### Outcome measures

All outcome measures will be administered by a study nurse entirely independently of the study physiotherapists. These measures will be taken at the first nurse home visit, following taking of written, informed consent, and again at the second and third nurse visits in weeks 6 and 12 of participants' involvement in the study. The outcome measures administered at all three time-points will be as follows:

#### Primary outcome measures - impairments

• Maximal isometric quadriceps strengths (continuous scale)

(measured in sitting at 90° knee flexion, using a Chatillon DFX-200 electronic dynamometer, stabilised against a wall, using a bespoke stabilisation rig (Additional file 4)).

• Degree of active end-range knee flexion (continuous scale).

(measured in supine on a portable examination couch, using a standard 10-inch universal perspex goniometer, with reference to the anatomical landmarks of the lateral malleolus of the ankle and the greater trochanter of the femur).

• The Four Balance Test Scale [27,28] (ordinal scale, range 0-5)

(tests the ability of the individual to balance in each of four postures for 10 seconds - feet together; semi-tandem stand; tandem stand and single leg stand).

• A modified version of Franchignoni et al's timed standing balance test [29,30] (continuous scale) (single-leg stance, hands on hips, up to a maximum of 30 seconds).

#### Secondary outcome measures - symptoms

• Self-report measures of pain, stiffness and physical function (WOMAC LK 3.1) [31].

• The persistence of knee pain symptoms (measured via one Likert response-type question) [32].

• The perceived 'bothersomeness' of the knee problem (measured via one Likert response-type question) [33].

In addition, the following secondary outcome measures, not gathered at baseline will be assessed at the 6 and 12 week nurse home visits:

• Global change in the knee problem (measured via Likert-response-type questions at 6 and 12 weeks) [34].

• Adherence to the exercise programme (measured via one Likert-response type question at 6 and 12 weeks, and via one free-text-response-type question at 12 weeks).

• Barriers to adherence to the exercise programmes, their acceptability and ways in which participants feel that they can be improved will be measured via two Likert-response-type questions and five free-text-response-type questions at 12-weeks only.

Additional information regarding adherence will be derived from the participant self-complete daily exercise diaries. Throughout the study, the study nurses taking the outcome measures will remain blinded to the impairment status of each of the participants.

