#### Sensitivity analyses

To explore the potential contribution of regression to the mean, data on the three impairment measures collected for our participants at the baseline, 3-year and 6-year clinical assessment study clinics [23] will be compared to the corresponding measures taken at the initial TargET-Knee-Pain study nurse visit.

To explore the contribution of potential ceiling effects (i.e. how much improvement can be possible in the comparison groups, who will inevitably be starting with higher measures for the given target impairments), a definition of "lack of impairment" for each of the three impairments will be derived, based on age-gender stratified norms. The percentage of individuals who lack each of the target impairments, according to these definitions, will be determined at 12-week follow-up, and will be compared between those who were and those who were not impaired in that measure at recruitment.

To explore the effects that poor adherence with the exercise programmes may have on the results, efficacy subgroup analyses will be conducted, whereby the analyses will be repeated in the subgroup of individuals deemed to have been adherent with the exercise programmes and compared with the subset deemed not to have been adherent. For this purpose, inadequate adherence will be defined as follows:

• Not having done any of the exercises at all in the course of at least one rolling calendar week throughout the 12 week period of their involvement in the study (according to the daily exercise diaries).

• Not having done any of the exercises at all on a cumulative total of 12 days throughout the 12 week period of their involvement in the study (according to the daily exercise diaries).

• Participant self-report of not having done their exercises as often as they were advised to in either the 6 or 12 week questionnaires.

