#### Secondary analyses

To investigate whether improvements in the target impairments are reflected in improvements in self-reported knee pain, stiffness and functional difficulties, mean changes (or their non-parametric equivalents, depending on the distribution of the change values) in the corresponding WOMAC subscale scores, between baseline and 12 weeks, will be calculated across all individuals, irrespective of which impairments they received exercises for. Associations between changes in the target impairments and changes in the WOMAC subscales will be examined by calculating Pearson's product-moment correlation coefficients (or their non-parametric equivalents, depending on the distribution of the change values).

To investigate whether improvements in self-report measures of pain, stiffness and physical function will be greater amongst those participants receiving exercises targeted at more than one impairment than amongst those participants receiving exercises targeted at only one impairment, mean differences in WOMAC change scores for the three subscales (or their non-parametric equivalents, depending on the distribution of the change values) will be calculated for both of these groups and compared across them.

To investigate the feasibility of this intervention and its acceptability to patients, responses to free-text and Likert-response-type questions will be analysed. This will include questions about barriers to adherence to the exercise programmes, and questions soliciting participants' views regarding participation in the study and the ways in which they believe that things could be improved. Analyses will include frequency counts of the various responses to Likert-type questions and a thematic analysis of free-text responses in the 12 week questionnaire.

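### Barriers and acceptability are asked at week 12 only, so participants who withdraw or are lost before that visit give no answers and the feasibility result may be too favourable (minor)

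*Protocol article*

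**What the plan says.** All references are to the Protocol article.

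- **Timing.** Under Secondary outcome measures - symptoms, barriers to adherence, acceptability and ways to improve the programmes "will be measured via two Likert-response-type questions and five free-text-response-type questions at 12-weeks only". Adherence is a separate item, "measured via one Likert-response type question at 6 and 12 weeks, and via one free-text-response-type question at 12 weeks".
- **Use.** Under Secondary analyses: "To investigate the feasibility of this intervention and its acceptability to patients, responses to free-text and Likert-response-type questions will be analysed". The methods are frequency counts of the Likert answers and "a thematic analysis of free-text responses in the 12 week questionnaire".
- **Who is visited.** Under Outcome measures, the nurse measures participants at the first home visit and "again at the second and third nurse visits in weeks 6 and 12 of participants' involvement in the study". The visits are scheduled by involvement in the study. They do not depend on still doing the exercises.
- **Non-adherers.** Under Sensitivity analyses, the analyses are repeated in adherers, who are "compared with the subset deemed not to have been adherent". One criterion for inadequate adherence is "Not having done any of the exercises at all in the course of at least one rolling calendar week".
- **Other records.** Under Interventions, the daily diaries have room for comments, and each physiotherapist contact is written up. The diaries are later named as a source on adherence. Neither source is named for the feasibility and acceptability analysis.

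**The concern.** Feasibility and acceptability are to be judged from answers collected at a single point, the last visit. Anyone who has left the study by then has no opportunity to answer. Leaving is unlikely to be unrelated to the question: pain, burden or dislike of the exercises are plausible reasons for withdrawal, and they are the barriers that the items are meant to capture. Frequency counts among those seen at week 12 would then lean towards the favourable side, and the thematic analysis would contain no account from those who withdrew.

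This differs from ordinary missing data in one respect. The timing is a stated rule of data collection, so no analysis plan can repair it later: an answer that was never requested cannot be recovered. At stake is the credibility of a descriptive secondary result that would inform how the programme is refined.

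**Working it through.** The plan states no figure on this point, so there is nothing to reproduce. The check has two parts.

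**1. Who gives an answer under the rule as written**

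| Participant | Seen by the nurse at week 12? | Answers the barrier and acceptability items? |
|---|---|---|
| Exercises throughout | Yes | Yes |
| Stops or lapses, stays in follow-up | Yes: visits follow involvement in the study, and non-adherers are a planned subset | Yes, from memory |
| Withdraws or is lost after week 6 | No | No; only the week-6 adherence item is available |
| Withdraws or is lost before week 6 | No | No |

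The gap is confined to the last two rows. It depends on loss from week-12 follow-up and not on stopping the exercises.

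**2. How large the effect could be**

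Input from the article: target sample N = 60 (Sample). Assumptions, since the article gives none of these: L people leave before week 12, a proportion p_R of responders find the programme acceptable, and a proportion p_L of leavers would have said so.

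Reported proportion = p_R. Proportion among all starters = [(60 − L) × p_R + L × p_L] / 60. The difference is therefore (L/60) × (p_R − p_L).

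With p_R = 0.90 and p_L = 0.30:

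- L = 0: 0.90, no bias.
- L = 5: (55 × 0.90 + 5 × 0.30)/60 = (49.5 + 1.5)/60 = 0.85.
- L = 10: (50 × 0.90 + 10 × 0.30)/60 = (45 + 3)/60 = 0.80.
- L = 15: (45 × 0.90 + 15 × 0.30)/60 = (40.5 + 4.5)/60 = 0.75.

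The result scales with the assumed gap. With p_L = 0.60 the gap halves to 0.30, and the overstatement is 2.5, 5 and 7.5 percentage points in place of 5, 10 and 15.

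Bounds that assume nothing about the leavers' views, with about 80% acceptability among responders:

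| Lost of 60 | Acceptable / responders | All lost find it unacceptable | All lost find it acceptable |
|---|---|---|---|
| 3 (5%) | 46/57 | 46/60 = 76.7% | 49/60 = 81.7% |
| 6 (10%) | 43/54 | 43/60 = 71.7% | 49/60 = 81.7% |
| 12 (20%) | 38/48 | 38/60 = 63.3% | 50/60 = 83.3% |
| 18 (30%) | 34/42 | 34/60 = 56.7% | 52/60 = 86.7% |

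With few losses the range is narrow. With 12 or more losses, the observed figure says little about all who started.

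**The case against.** Several points count against making much of this.

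- **Stopping the exercises is not leaving the study.** A reader might infer that anyone who gives up the programme is never asked, so that the answers come from people who completed the exercises. The article does not support that. Nurse visits are tied to involvement in the study, non-adherers are a planned analysis subset, and inadequate adherence is partly defined by self-report in the 6- or 12-week questionnaire. Non-adherers are thus expected to complete it. This stands fully. What remains for those who stay is a recall problem: someone who stopped at week 3 is asked about nine weeks later.
- **The questionnaire is not the only trace.** The week-6 adherence item, the diary comments and the physiotherapist records would hold some information on people who leave, so their reasons are not shown to be lost altogether. This stands in part: the Secondary analyses section does not draw on the diaries or the physiotherapist records for acceptability.
- **An exit form may exist in the full protocol.** An article commonly leaves the handling of withdrawals to the full document, and silence there is no finding. This stands for the silence, but the limit to week 12 is stated outright, and the thematic analysis is tied to the 12-week questionnaire.
- **The decision on further testing does not rest on acceptability.** A reader might infer that the bias would distort the decision to proceed to a randomised trial. The Discussion bases that decision on efficacy, and the aims in the Background concern impairments and symptoms. This stands, and it keeps the point minor.
- **The entry criterion adds little.** The requirement that "individuals must be willing and able to commit to a programme of exercises for a 12-week period" affects who is recruited. It does not bear on when the questions are asked.

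**Conclusion.** The point holds in a limited form. The items are fixed at week 12, and the planned feasibility analysis depends on them. Participants who withdraw or are lost before the third nurse visit therefore contribute no answers on barriers, acceptability or improvements. If these people liked the programme less than those who stayed, the result is too favourable.

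The size is unknown because the article gives no expected loss. Under the assumptions shown (90% among responders, 30% among leavers), 5 to 15 leavers of 60 overstate acceptability by 5 to 15 percentage points. With no loss, or with leavers who hold the same views as responders, there is no bias. The direction rests on a plausible assumption about why people leave, which the article neither supports nor contradicts.

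Severity is minor: the result is secondary and descriptive, the primary analyses are untouched, and the improvement is cheap.

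**What to change.** In Secondary outcome measures - symptoms, replace the restriction to week 12 with: *at 12 weeks, or at withdrawal if earlier*. Use the same two Likert and five free-text questions. Send the form by post, or have it taken by telephone by someone other than the treating physiotherapist. The article keeps outcome collection separate from the physiotherapists, and people may be reluctant to criticise a programme to the therapist who delivers it.

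In Secondary analyses, state that the report will give the number who answered out of all who started, and will show withdrawal answers separately from week-12 answers. The two should not be pooled as last available answers, because they reflect different lengths of exposure to the programme. Extend the thematic analysis to the free text on the withdrawal forms.

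Cost: one short form and a few words of text. Some leavers will decline, so the gap will narrow without closing, and reporting the number of responders out of all starters will show how much remains.
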